**Statistical Analysis**

We will measure an incidence rate ratio for the association between GTZ use and incident PD using poisson regression, comparing patients exposed to GTZs with patients exposed to alternative treatments. The primary analysis will follow all patients from their index date until the earliest of a PD record, transfer out/death, or last collection date for the practice, and their exposure will remain as defined at the index date, regardless of any subsequent changes in therapy (analogous to an intention to treat analysis in a clinical trial). Secondary analyses will be as follows:

- Censoring follow up at end of GTZ therapy, defined as last prescription plus 90 days, followed by at least 180 days GTZ-free follow up time.
- Stratified analysis based on metformin and GTZ treatment status, to explore the individual and any additive effects of both treatments. Whilst we anticipate most patients will be exposed to metformin, we anticipate a sizeable population who will not receive metformin.
- We have chosen to measure the incidence of PD from the start of therapy with GTZs as the pre-clinical work to date suggests a fast onset of any protective effect. Whether this effect varies with exposure length will be assessed through a stratified analysis on length of follow up after starting GTZ therapy.
- Sensitivity analysis defining PD as a Readcode indicating PD plus at least 2 prescriptions for an anti-Parkinson’s drug, to reduce the likelihood of outcome misclassification. Although cases with little follow up beyond their diagnosis will be excluded, this approach will only reduce study power, but will reduce misclassification bias. The date of earliest recorded diagnosis will remain the date of the outcome.
- Sensitivity analysis to look separately at the effects of pioglitazone and rosiglitazone.
- Sensitivity analysis adjusting for all variables identified as potential confounders, in addition to those included in the forward stepwise modelling strategy (see below).

Adjustments for potential confounding will be made in a forward stepwise manner retaining variables in the model if they have a substantial impact on the estimated rate ratio (a change of 10% or more), and starting with variables that have the greatest effect on PD incidence in univariate analyses. All data management and analyses will be performed using Stata 12 (StataCorp, Texas).

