**Study Population**

The study population will be drawn from the entire CPRD population with acceptable up to standard (UTS) follow up time. People will be selected for inclusion if they have received any prescription for a GTZ antidiabetic (code list in Appendix 1), with the first occurrence being at least 12 months after the patient’s start of UTS follow up. This is to increase the likelihood that we are studying new users of GTZs, which will be of importance when we assess any effect of treatment duration on PD risk. Eligibility will begin in 1999 when the first GTZ was launched. No age restrictions will be applied to eligibility; the mean age of type 2 diabetes diagnosis in a US population was ~ 46 years in 2000 (Koopman et al, 2005) and so we anticipate the age profile of patients receiving GTZ antidiabetics will be a little younger than the typical onset age for PD (over 50 year), making them an ideal group in which to study the long term effects of a potentially neuroprotective agent. Potential participants with any diagnosis of PD prior to their first GTZ prescription will be excluded. Users will be classified according to their diabetes treatment stage at the time the GTZ is started, as follows:

1. GTZ monotherapy, no prior oral anti-diabetic (OAD)
2. GTZ monotherapy, previous OAD discontinued
3. Combined OAD therapy, GTZ being taken with other OADs

A feasibility count shows there are ~43,000 incident GTZ users with at least 12 months prior UTS follow up. Follow up for the study analysis will begin at the first prescription for a GTZ and end at the earliest of last collection date for the practice, patient transfer out or death date.

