**Power Calculation**

Amongst the 43,000 GTZ exposed patients identified for the feasibility count, 144 were first diagnosed with PD after starting a GTZ. Using STATA 12, we estimate we will have 99% power to detect a 30% reduction in PD incidence amongst GTZ users, if we match each exposed patient to five unexposed. Power to detect a 25% and 20% reduction will be and 91% and 71% respectively. We believe an effect size of 25% would represent a clinically meaningful association, and may also be plausible, given the near complete protection identified in animal studies (Sadeghian et al, 2012).

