**Exposures, Outcomes and Covariates**

Exposure will be determined by prescribing records, using code lists for individual OADs. Code lists for GTZs can be found in Appendix 1. The index date for each patient will be their first prescribing event that qualifies them for study entry (e.g. first exposure to a GTZ)

The outcome for this study is the first recording of a PD diagnosis after the index date, as identified from clinical and referral records, using the Read code list in Appendix 2. PD due to known causes will be excluded based on the recording of codes presented in Appendix 2.

Covariates to be explored due to their possible association with PD and potential confounding nature will be:

- Smoking status determined using the additional clinical details file
- HRT use determined using prescribing records
- Head trauma as determined by Read code recording
- Age and sex will be accounted for through matching
- Calcium channel blocker use as determined by prescribing records: This exposure has been shown to reduce the incidence of PD (Becker et al, 2008).
- Diabetes itself has been shown to be possibly associated with PD (Wahlqvist et al, 2012). Length of time between diabetes diagnosis and index date, and HbA1c level at index date will be determined and explored for possible confounding properties. In addition, the effect of time updated HbA1c levels will be explored.
- Metformin has been suggested to also have a protective effect against PD (Wahlqvist et al, 2012). As a very commonly prescribed diabetes medication, this will be explored in detail as described below under “Statistical Analysis”.

Other covariates that have not been shown to be associated with PD will also be explored in case of possible confounding, and will include:

- Alcohol consumption
- Body mass index
- Calendar year

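### The on-treatment censoring rule can make end of glitazone therapy depend on whether PD is recorded in the next 180 days, and it states no rule for comparators

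*Protocol*

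**What the plan says.** The Statistical Analysis section of the Protocol plans an "incidence rate ratio for the association between GTZ use and incident PD using poisson regression". The primary analysis keeps exposure as it was at the index date and runs to "the earliest of a PD record, transfer out/death, or last collection date for the practice".

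The first secondary analysis is an on-treatment one. It censors at the end of glitazone therapy, "defined as last prescription plus 90 days, followed by at least 180 days GTZ-free follow up time". Therapy is thus declared ended at day 90 after the last prescription only if 180 more glitazone-free days of follow-up are then observed, that is, to day 270.

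The Study Population section defines follow-up differently. There it will "end at the earliest of last collection date for the practice, patient transfer out or death date", and a PD record is not on the list.

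The censoring rule names glitazone therapy only. The protocol states neither an end-of-therapy rule for the comparator drug nor what happens when a comparator starts a glitazone. On age, the Exposures, Outcomes and Covariates section says: "Age and sex will be accounted for through matching".

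**The concern.** A censoring rule must not depend on the outcome it is used to study. If follow-up stops at PD, whether a patient is censored at day 90 depends on whether PD is recorded during the next 180 days. Events from that window enter the numerator, while nearly all the matching event-free time is left out of the denominator. The glitazone rate is then too high, and a real protective effect would look weaker than it is.

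This is the only listed analysis that explicitly ends follow-up when glitazone therapy ends, so readers will look to it for the effect while on the drug. Stopping will be common: the Selection of Comparison Group section records that rosiglitazone was suspended and that pioglitazone use declined.

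Secondly, if only the glitazone arm is cut short, its person-time comes from earlier in follow-up, at younger attained ages, than comparator person-time. Matching on age at entry does not correct that.

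**Working it through.** **The plan's own figures.** The protocol gives no figure for this rule. The nearest benchmark is its power statement: "Amongst the 43,000 GTZ exposed patients identified for the feasibility count, 144 were first diagnosed with PD after starting a GTZ". The exposed risk is 144/43,000 = 0.00335. Taking the unexposed risk as 0.00335/RR, 1:5 matching and an assumed two-sided 5% level, a two-proportion calculation gives 99.0%, 92.0% and 71.8% power for reductions of 30%, 25% and 20%. With a continuity correction it gives 98.9%, 91.3% and 70.3%. The stated 99%, 91% and 71% are reproduced. The Power Calculation section names a 25% reduction as clinically meaningful, so a true ratio of 0.75 is the yardstick below.

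**Two patients under the rule, if follow-up stops at PD.** Count days from the last glitazone prescription.
- PD recorded on day 150: follow-up after day 90 is 60 days, short of 180. The patient is not censored and contributes 150 days and one on-treatment event.
- No PD, observed past day 270: censored at day 90, contributing 90 days and no event. Days 90 to 270 are dropped.

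**Approximate size.** The events wrongly kept are about (PD rate) × (share of patients stopping and observable to day 270) × 180/365.25 years. Dividing by on-treatment events gives

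inflation ≈ 1 + share × 0.493 / (mean on-treatment years).

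For example, with mean duration 3 years and maximum follow-up 8 years: 1 + 0.54 × 0.493/2.04 = 1.13.

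**Simulation with no drug effect.** These assumptions are not in the protocol: exponential time to last prescription with mean 1 to 5 years, administrative follow-up up to 8 or 12 years, and 5% per year lost or dead. The PD rate was set at 0.0035 per year for precision and was either constant or rising 8% per year. There were 4 million patients per scenario. Restarts after a gap were not simulated.

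| Mean duration / max. follow-up (years) | Share stopping | On-treatment years | Formula | Simulated inflation from 180-day condition (constant rate) | One-arm censoring alone (rising rate) | Both together (rising rate) |
|---|---|---|---|---|---|---|
| 1 / 8 | 0.77 | 1.09 | 1.35 | 1.345 | 0.868 | 1.180 |
| 1 / 12 | 0.82 | 1.12 | 1.36 | 1.346 | 0.789 | 1.072 |
| 2 / 8 | 0.64 | 1.66 | 1.19 | 1.187 | 0.912 | 1.086 |
| 2 / 12 | 0.72 | 1.78 | 1.20 | 1.198 | 0.837 | 1.005 |
| 3 / 8 | 0.54 | 2.04 | 1.13 | 1.129 | 0.933 | 1.054 |
| 3 / 12 | 0.63 | 2.28 | 1.14 | 1.132 | 0.863 | 0.983 |
| 5 / 8 | 0.40 | 2.51 | 1.08 | 1.080 | 0.956 | 1.033 |
| 5 / 12 | 0.50 | 2.95 | 1.08 | 1.083 | 0.906 | 0.983 |

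- With the rising rate, the inflation from the 180-day condition is almost the same, 1.081 to 1.359. The overall range is therefore 1.08 to 1.36.
- If follow-up continues past PD, the inflation factor is 1.00 in every scenario.
- If everyone is censored at last prescription plus 90 days, the ratio to uncensored comparators with a constant rate is 0.997 to 1.014, which is 1.00 within simulation error.
- With both mechanisms and a constant rate, the ratio is 1.08 to 1.37.
- A separate run at 0.7 PD cases per 1,000 person-years (follow-up uniform 2 to 12 years, deaths 4% per year, 20 million patients per scenario) gave inflation of 1.27, 1.16 and 1.10 at mean durations of 1.5, 2.5 and 4 years. The higher rate used in the table is therefore not driving the result.

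**Against the yardstick.** Suppose the 180-day condition acts alone and the drug effect persists through the window. A true 0.75 would then appear as 0.75 × 1.08 = 0.81 at a mean duration of 5 years, 0.75 × 1.13 = 0.85 at 3 years, and 0.75 × 1.35 = 1.01 at 1 year.

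**The case against.** The rule asks for glitazone-free time, not PD-free time. A reader might infer that it plainly requires 180 PD-free days, but that follows only if the primary analysis's end of follow-up is carried over. Two places point the other way. The Study Population section does not list PD as an end of follow-up. The sensitivity analysis that requires anti-Parkinson's prescriptions also speaks of follow-up after diagnosis and relies on prescriptions written then. If the 180 days mean time under observation, a user with PD on day 150 can still complete them, is censored at day 90, and the bias disappears. This objection stands in full. What remains is that the protocol supports two codings with materially different results.

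A reader might also infer that comparators run uncensored. The protocol does not say so; it is silent, and a separate analysis plan could supply the rule. Unequal follow-up does not by itself bias a rate ratio: with a constant rate the simulation gives about 1.00. Bias needs a PD rate that changes over follow-up and is left unmodelled, or stopping that is related to PD risk. Calendar year is among the covariates, and a stratification by length of follow-up is planned. Both bear on changing rates, though neither replaces attained age.

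Finally, the sizes rest on assumed durations and rates, and the two mechanisms oppose each other. That is correct and limits what can be claimed.

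**Conclusion.** The point holds conditionally, at moderate severity, for this one secondary analysis.

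If follow-up stops at PD, the 180-day condition makes censoring depend on the outcome and inflates the glitazone rate by about 8% to 36% under no effect, for assumed mean durations of 5 years down to 1 year. If follow-up continues past PD, that bias is nil. If comparators are also left uncensored, PD incidence rises by an assumed 8% per year and attained age is not modelled, one-arm censoring alone moves a null ratio to 0.79 to 0.96.

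It is tempting to conclude that the on-treatment ratio is certainly biased, or that it will hide protection. The protocol does not support either. It gives no treatment duration or stopping rate, and the two mechanisms together give 0.98 to 1.18 with the rising rate, which includes almost no net bias. The primary analysis keeps exposure as defined at index and is not touched.

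**What to change.** Reconcile the two definitions of end of follow-up, and reword the rule so that it cannot depend on the outcome:
- Identify the glitazone-free gap from prescribing records alone: therapy has ended when no further glitazone prescription appears within 270 days of the last one (90 + 180), regardless of any PD record, death or end of data in that gap. The gap has to be defined in this way once the follow-up condition is removed, or an ordinary late refill could end therapy.
- Always end on-treatment follow-up at that last prescription plus 90 days, or at the end of follow-up if earlier.
- Count PD only if it is recorded on or before that date.
- Apply a parallel rule to comparators: end of their qualifying oral antidiabetic therapy plus 90 days, or first glitazone prescription if earlier.
- Adjust for attained age, not only matched age at entry.

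This removes the look-ahead under either definition of follow-up. It does not cure stopping that is itself related to PD risk, which should be acknowledged as a limitation. The cost is a few sentences, a few lines of code and the loss of some on-treatment events.

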**Study Type**

This is a hypothesis testing study

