**Limitations of the Study Design, Data Sources and Analytic Methods**

Diagnoses of PD in the CPRD have a positive predictive value of 90% (Becker et al, 2008) and so a small degree of misclassification amongst outcomes is expected. However, this is likely to be non-differential with respect to GTZ exposure and would be expected to bias results towards the null. In addition, missing cases of PD are likely to be rare in our study population, given that the prevalence of PD is low in the general population. Misclassification of the exposure is also likely to occur to some degree, with patients not being completely adherent to prescribed medicines. However, diabetes is a serious condition for which patients are likely to be motivated to take their medication, and substantial misclassification is not anticipated. Again, misclassification is unlikely to be differential with respect to PD status and so a dilution of any effect towards the null would be expected.

Whilst a small number of risk factors for PD are known and will be accounted for in the design and analysis (e.g. age, sex, smoking), it is not anticipated that these factors will be strongly associated with the choice to prescribe a GTZ, and so confounding is not expected to be strong in this study. Nonetheless, the analysis plan ensures potential confounding will be addressed, and in particular the separate and potentially additive effects of GTZs and metformin will be assessed.

Since the study is conducted entirely within the population with diabetes, the generalisability of results may be affected. However, it is unlikely that any pharmacological effect of GTZs relevant to PD would be limited to people with diabetes only.

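### Two effect-modification questions (length of follow-up, and metformin) are given only a stratified analysis, which does not test whether the strata differ (minor)

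*Protocol*

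**What the plan says.** The Statistical Analysis section of the protocol names one primary analysis, the overall comparison with exposure fixed at the index date: "We will measure an incidence rate ratio for the association between GTZ use and incident PD using poisson regression". The rest of the list is introduced by "Secondary analyses will be as follows". Two entries ask about effect modification:

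- Metformin: "Stratified analysis based on metformin and GTZ treatment status, to explore the individual and any additive effects of both treatments". The Limitations section relies on this entry when it says that "in particular the separate and potentially additive effects of GTZs and metformin will be assessed".
- Follow-up length: "Whether this effect varies with exposure length will be assessed through a stratified analysis on length of follow up after starting GTZ therapy".

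Neither entry names an interaction term, a heterogeneity or trend test, or a rule for comparing strata. No follow-up bands are given. On the metformin split the protocol says only: "Whilst we anticipate most patients will be exposed to metformin, we anticipate a sizeable population who will not receive metformin". The Power Calculation section covers the overall comparison alone.

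**The concern.** Whether an effect varies is a question about the difference between stratum-specific rate ratios. A stratified analysis supplies the separate ratios and leaves the comparison to the eye, usually to which stratum reaches significance. That guide is poor when events are few and the strata differ in size.

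The metformin question has a second gap. The planned model estimates rate ratios, so its natural null for joint action is multiplicative, while the stated question is about additive effects. The two scales can give different answers on the same data.

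Neither question is incidental. The Study design section presents the study of change over time as a benefit of the cohort design, and Study Population ties new-user selection to the treatment-duration question. Background & Rationale expects the results to guide where further clinical research goes. An apparent benefit only with metformin, or only after some years, could steer that choice even if it arose by chance.

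**Working it through.** **Inputs from the protocol (Power Calculation):** 43,000 exposed patients, 144 exposed events, five unexposed per exposed, and stated power of 99%, 91% and 71% for reductions of 30%, 25% and 20%.

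**Assumptions:** two-sided 5% level (not stated); no-metformin share of 10% to 50%; three follow-up bands with equal events; person-time in ratio 5:1 in every stratum.

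**1. Reproducing the stated power.** Two-proportion test, exposed risk 144/43,000, unexposed risk 144/(43,000 × RR), 43,000 against 215,000 patients. For RR 0.70, 0.75 and 0.80 this gives 99.0%, 92.0% and 71.8%; with continuity correction 98.9%, 91.3% and 70.3%. The stated figures are reproduced to within about one point, which supports the 5% two-sided assumption.

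**2. Metformin strata, true RR 0.75 in both.** Exposed events total 144 and unexposed events 720/0.75 = 960, split by the no-metformin share f. In each stratum the variance of ln RR is 1/(exposed events) + 1/(unexposed events), and power is Φ(|ln RR|/se − 1.96) plus the small opposite tail. With stratum powers p1 and p2, the chance that exactly one stratum is significant is p1(1 − p2) + p2(1 − p1).

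Example, f = 0.10:
- With metformin: 1/129.6 + 1/864 = 0.00887, se 0.0942, power 0.863.
- Without: 1/14.4 + 1/96 = 0.0799, se 0.283, power 0.175.
- Discordant: 0.863 × 0.825 + 0.175 × 0.137 = 0.736.

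| No-metformin share | Power, with metformin | Power, without | Exactly one significant |
|---|---|---|---|
| 10% | 0.863 | 0.175 | 74% |
| 20% | 0.821 | 0.302 | 63% |
| 30% | 0.768 | 0.422 | 54% |
| 50% | 0.624 | 0.624 | 47% |

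If the 144 is instead taken as the count expected with no effect (108 exposed and 720 unexposed events at RR 0.75), the last column becomes 68%, 61%, 55% and 50%. The message does not change.

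**3. Three equal follow-up bands, true RR 0.75 in each.** Each band has 144/3 = 48 exposed and 960/3 = 320 unexposed events. Variance 1/48 + 1/320 = 0.0240, se 0.155, |ln 0.75|/se = 0.2877/0.155 = 1.86, power about 0.46. The chance that the bands do not all agree is 1 − 0.46³ − 0.54³ = 1 − 0.097 − 0.157 ≈ 0.75.

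**4. Interaction test on the same data.** With a uniform effect it rejects 5% of the time. To see its power, take RR 0.75 with metformin and 1.00 without; the variance of the log ratio of rate ratios is the sum of 1/events over four cells. At f = 0.50: 1/72 + 1/480 + 1/72 + 1/360 = 0.0326, se 0.181, 0.2877/0.181 = 1.59, power 36%. For f = 10%, 20% and 30% the power is 16%, 24% and 31%. The ratio of rate ratios detectable with 80% power is about 2.3, 1.9, 1.7 and 1.7 for f = 10%, 20%, 30% and 50%.

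**5. Why the scale matters.** Purely as illustration, let each drug alone have rate ratio 0.75. Exactly multiplicative joint action gives 0.75 × 0.75 = 0.5625. Exactly additive action gives 0.75 + 0.75 − 1 = 0.50. With a joint ratio of 0.5625 there is no interaction on the ratio scale, but on the additive scale RERI = 0.5625 − 0.75 − 0.75 + 1 = 0.0625.

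**The case against.** The strongest reply is that these are secondary analyses under one named primary analysis, and that the metformin sentence itself says its aim is to explore. Stratifying on both metformin and GTZ status can also be read as a four-group comparison in one model, and nothing excludes an interaction term. Nowhere does the protocol say that a difference will be concluded because one stratum is significant and another is not. The discordance figures therefore measure a risk that the plan leaves open, not an error it commits to. They also rest on splits that the protocol does not give. Interaction tests are often left to a statistical analysis plan, and the low power in step 4 means that such a test will often miss real variation.

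Most of this stands, and it limits the point to a minor one. It does not remove it. For follow-up length the protocol does name the method by which variation will be judged, and that method does not answer the question. For metformin, even the four-group reading needs a stated contrast and scale. Deferral is also a weaker defence here than usual: the protocol's content checklist marks the statistical analysis plan as included, and the covariates section sends the reader to Statistical Analysis for the detail on metformin.

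Three stronger readings are tempting and are not supported:

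- From "This is a hypothesis testing study" a reader might infer that every stratum result is confirmatory. That line describes the study as a whole; the primary and secondary ranking is clear, and no hypothesis about effect modification is stated.
- From "Sensitivity analysis to look separately at the effects of pioglitazone and rosiglitazone" a reader might infer an untested comparison of the two drugs. The text promises two separate estimates and no comparison between them.
- A reader might count the strata as extra formal tests and compute a familywise error rate. The protocol assigns them no significance rule, and the number of strata would have to be assumed.

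**Conclusion.** The point holds in a limited form and is minor. The protocol asks whether the GTZ effect varies with follow-up length and whether GTZ and metformin act additively, and for both it states only a stratified analysis, which does not test a difference. Under a uniform rate ratio of 0.75, disagreement on significance is close to a coin toss or more likely: about 47% to 74% between metformin strata and about 75% across three bands, against 5% for an interaction test. These figures depend on the assumed metformin share, the assumed equal bands, the 5% two-sided level and the 144 events from the feasibility count. That chance differences will actually be reported as real is not something the document shows; it only lacks a safeguard against it. The primary rate ratio is not affected.

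**What to change.** In Statistical Analysis:

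- **Follow-up length.** Split person-time into pre-stated bands and fit a GTZ-by-band interaction in the Poisson model on the full cohort. Report the ratios of rate ratios with 95% confidence intervals and the interaction test.
- **Metformin.** Fit a GTZ-by-metformin interaction and report it in the same way. Show the four groups (neither, each alone, both) against a common reference, with an additive-scale measure such as RERI and its confidence interval, because additivity is the stated question.
- **Interpretation.** Base any statement that the effect varies on these estimates and tests, not on which stratum is significant. Keep the stratum-specific rate ratios as description.
- **Status.** Say that these secondary analyses are exploratory and have low power to detect interaction.

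The cost is a few sentences and some extra model terms, with no new data. The downside is that claims about differences between strata will be weaker: power is only about 16% to 36% for 0.75 against 1.00. A non-significant interaction must not be read as proof that the effect is uniform.

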**Selection of Comparison Group**

Each GTZ exposed patient will be matched by age, sex, and practice with up to 5 patients receiving other oral treatment for diabetes (unexposed group). To reduce the possibility of confounding, we will only select patients who have also received oral antidiabetic treatments, thus reducing the difference in disease stage between GTZ users and non-users. GTZ prescribing has evolved during >10 years according to changes in treatment guidance and changes made to the licensed indication. Initially they were mostly used as second line combination treatment, but were subsequently also used at earlier stages of diabetes treatment. Rosiglitazone was eventually suspended due to cardiovascular safety concerns and pioglitazone use has waned due to concerns over the risk of bladder cancer. To be considered for inclusion, only patients present in the database from 1999 onwards and with at least 12 months UTS follow up prior to prescribing events that trigger eligibility will be included. For instance a patient could be matched to a GTZ user in category 1) above if they had never received an OAD before 1999 and began taking a sulphonylurea with no other OAD after at least 12 months UTS follow up. Follow up for the unexposed will begin at the first prescribing event that makes them eligible for inclusion.

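### Metformin's individual effect is promised, but the stated age and sex control is matching on glitazone exposure, which does not balance metformin users against non-users

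*Protocol*

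**What the plan says.** The only objective is the rate ratio for Parkinson's disease (PD) comparing glitazone users with patients on other agents. Metformin enters as a secondary item under Statistical Analysis: "Stratified analysis based on metformin and GTZ treatment status, to explore the individual and any additive effects of both treatments". The Limitations section then offers this analysis as part of the assurance on confounding, saying that "in particular the separate and potentially additive effects of GTZs and metformin will be assessed".

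Three statements determine how confounding is controlled.

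- **Matching** (Selection of Comparison Group) is organised by glitazone exposure: "Each GTZ exposed patient will be matched by age, sex, and practice with up to 5 patients receiving other oral treatment for diabetes".
- **Age and sex** (Exposures, Outcomes and Covariates): "Age and sex will be accounted for through matching".
- **Model and covariate rule** (Statistical Analysis): "We will measure an incidence rate ratio for the association between GTZ use and incident PD using poisson regression", with forward selection "retaining variables in the model if they have a substantial impact on the estimated rate ratio (a change of 10% or more".

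There is also a "Sensitivity analysis adjusting for all variables identified as potential confounders, in addition to those included in the forward stepwise modelling strategy". The Limitations section says, in general terms, that known risk factors are dealt with in both design and analysis, and gives age, sex and smoking as examples.

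**The concern.** Matching balances the two groups that were matched. Here these are glitazone users and comparators. A contrast of metformin users with non-users cuts across that division and gains no age, sex or practice balance from it. Once patients are split by metformin status, a glitazone user and the matched comparators can fall into different strata, so balance is no longer guaranteed even for the glitazone comparison within a stratum.

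The covariate rule may not repair this. The plan defines one rate ratio, for glitazones. Judged on that ratio, a variable that is balanced across glitazone groups changes nothing and is not retained, however strongly it differs by metformin use.

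The plan sets no age limits and PD is a disease of later life, so age is the obvious candidate. At stake is whether a reported metformin effect, or a combined effect in patients on both drugs, reflects the drug or only the age of those who receive it.

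**Working it through.** **1. The plan's own figure.** The Power Calculation gives 99%, 91% and 71% power for reductions of 30%, 25% and 20%. Inputs: 43,000 exposed, 144 events, five comparators each, and two-sided alpha 0.05 (not stated, assumed). Take p1 = 144/43,000 = 0.00335 as the risk in glitazone users and p2 = p1/RR in comparators. Power = Φ[(p2 − p1 − 1.96·SE0)/SE1], where SE0 is the pooled and SE1 the unpooled standard error of the difference.

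| RR | p2 | Power found | Power stated |
|---|---|---|---|
| 0.70 | 0.00478 | 99.0% | 99% |
| 0.75 | 0.00447 | 92.0% | 91% |
| 0.80 | 0.00419 | 71.8% | 71% |

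The figures reproduce to within about one percentage point. They concern the glitazone contrast only, so they neither support nor weaken this point. They do supply a yardstick: the plan calls a 25% effect (RR 0.75) clinically meaningful for glitazones.

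**2. What an age gap alone does to a metformin ratio.** The Protocol gives neither ages by metformin status nor an age gradient for PD, so both are assumed. Suppose metformin has no effect, incidence doubles every D years of age, and the two age distributions have the same shape but lie G years apart. The unadjusted ratio is then 2^(−G/D) if non-users are older and 2^(G/D) if users are older.

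| G (years) | D (years) | Non-users older | Users older |
|---|---|---|---|
| 3 | 10 | 2^(−0.3) = 0.81 | 1.23 |
| 5 | 10 | 2^(−0.5) = 0.71 | 1.41 |
| 8 | 10 | 2^(−0.8) = 0.57 | 1.74 |
| 5 | 7 | 2^(−5/7) = 0.61 | 1.64 |
| 5 | 15 | 2^(−1/3) = 0.79 | 1.26 |

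With D = 10, the gap that produces RR 0.75 is 10 × log2(1/0.75) = 4.2 years. Stated as a yearly rise g, the ratio is (1 + g)^(−G). For g from 5% to 12% and G from 3 to 5 years it runs from 1.05^(−3) = 0.86 to 1.12^(−5) = 0.57.

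**3. Would the 10% rule bring age in?** In a cohort matched on age by glitazone exposure, the age distribution is the same in both groups. Adding age therefore leaves the overall glitazone ratio where it was. This was checked by Poisson regression on expected counts, with no true effect of either drug, metformin use falling with age, a mean gap of 3.3 to 5.3 years and g of 5% to 10%:

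- metformin ratio without age: 0.85 to 0.62;
- metformin ratio with age: 1.00;
- change in the overall glitazone ratio on adding age: 0.0%;
- change in the glitazone ratio, in a model with both drugs and metformin use also differing by glitazone group (log-odds ±0.7): at most 7.4%.

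In every scenario run the change stays below 10%, so a rule judged on the glitazone ratio would leave age out while the metformin ratio stays biased.

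**The case against.** A reader might infer that the metformin contrast has no confounding control at all. The Protocol does not support that. Every patient is on oral diabetes treatment. Smoking, diabetes duration, HbA1c, BMI, calendar year and other variables are candidate covariates. A sensitivity analysis adjusts for all potential confounders whatever the 10% rule does. The Limitations section names age and sex as handled in the analysis as well as the design. This stands, and it narrows the point. But none of these provisions is said to apply to the metformin contrast, and the only specific statement on age and sex assigns them to matching. A general mention of analysis does not put an age term in this model.

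The rule's rate ratio could also mean each analysis's own ratio, since the paragraph follows the list of secondary analyses. On that reading a strong metformin confounder among the candidates would be kept. The text allows this, but age would still have to be a candidate, and it is the matching that is said to deal with it. An analysis conditional on matched set could carry some age control into metformin comparisons within a set; the plan names only Poisson regression.

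It is also tempting to conclude that the bias will look like protection. The Protocol has no data on the sign or size of the age gap, and if metformin users are older the bias reverses.

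Finally, this is an exploratory secondary analysis, and model detail may properly sit in an analysis plan that is not shown. The point is therefore not that a covariate list is absent. It is that the stated means of handling age and sex does not suit one of the contrasts the Protocol promises and relies on.

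**Conclusion.** The point holds in limited form. The matching, and a 10% rule judged on the glitazone ratio, do not protect the promised individual effect of metformin from confounding by age and sex. The other provisions may give partial control but are not tied to this contrast.

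The possible size is material: on the assumed doubling every 10 years, a gap of about 4 years is enough to imitate a 25% reduction. These figures show how sensitive the estimate is; they do not predict a bias, because the gap, its direction and the gradient are all assumed, and they apply only if age is left out of the model.

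The primary glitazone result is not affected. The glitazone ratio in a model with both drugs moved by at most 7.4% in the scenarios run.

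**What to change.** For this secondary analysis, specify one Poisson model with a four-level variable fixed at index: neither drug, metformin only, glitazone only, both. Force in age and sex, and preferably index year, diabetes duration, HbA1c at index and smoking, whatever they do to the glitazone ratio.

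Do not force in treatment stage. Under Study Population, stages 1 and 2 are glitazone monotherapy, so the both-drugs level is empty there at index, and stage partly restates metformin status.

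Alternatively, drop the claim to metformin's individual effect and report only the glitazone ratio within metformin strata, adjusted for age and sex.

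Either way, reword the assurance in the Limitations section to match. The cost is a short wording change and a few more terms in one secondary model. The variables are already to be collected or derived under the plan, and the primary analysis does not change.
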